**Figure 1 fig1:**
[figure not shown]
Flow chart of the research program.

## Methods: subjects, interventions, and outcomes

### Study setting

This prospective, multicenter, open cohort study will include HBV-infected patients from four large tertiary hospitals in North China. A total of 200 participants are planned, comprising 100 patients with CHB and 100 patients with CHB combined with MAFLD. We used the SPIRIT checklist when writing our report (17). The Institutional Review Board of Beijing You’an Hospital affiliated with Capital Medical University approved the trial protocol (version 9.1, reference number LL-2024-051-K, dated May 10, 2024).

### Eligibility criteria

Inclusion Criteria:

Chronic Hepatitis B (CHB): Meets the 2022 Guidelines for the Management of Chronic Hepatitis B: (1) HBsAg positive for >6 months; (2) On NA treatment; (3) HBsAg <1,500 IU/mL; (4) HBeAg negative; (5) HBV DNA <10 IU/mL.Metabolism-Associated Fatty Liver Disease (MAFLD):

(1) Diagnosis of hepatic steatosis confirmed by abdominal ultrasound, Fibroscan, or liver steatosis measurement via MRI. Steatosis is categorized as mild, moderate, or severe based on the thresholds of the above tests. (2) Additionally, the patient must meet one of the following three conditions: ①. Overweight or obesity (BMI ≥ 23 kg/m^2^); ②. Diabetes mellitus; ③. Lean or normal-weight patients meeting at least 2 metabolic abnormalities (e.g., Figure 2).

**Figure 2 fig2:**
[figure not shown]
MAFLD diagnostic process and criteria.

Exclusion Criteria: (1) Patients with combined HCV infection or autoimmune liver disease; (2) History of heavy alcohol consumption (alcohol intake >210 g/day for men and > 140 g/day for women); (3) Drug-induced secondary hepatic steatosis (e.g., tamoxifen, hormones); (4) Pregnant or lactating women, and those planning to conceive shortly; (5) Patients with a history of or current cirrhosis or hepatocellular carcinoma; (6) Comorbidities with other serious diseases that may affect nutritional status, such as malignant tumors, severe cardiac, pulmonary, renal, or other organic or psychiatric diseases; (7) Neutrophil counts <2 × 10^9^/L and/or platelet counts <80 × 10^9^/L, and total bilirubin >34 μmol/L before treatment.

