### Sample size

Since there are no existing literature reports on Peg-IFN treatment for combined MAFLD in the CHB-advantaged population, the sample size for this study is based on the results of our team’s previous research. In that study, Peg-IFN treatment of CHB and CHB combined with MAFLD patients for 48 weeks resulted in HBsAg clearance rates of 35 and 60%, respectively. Given the lack of established data in this specific population, we chose to use this estimate as it is reflective of our previous work, which involved similar patient profiles and treatment conditions. Setting the test level at *α* = 0.05 and the power of the study (1-*β*) at 0.90, the required sample size was calculated using the test module for two independent sample rates in PASS 11.0. The calculation indicated that 79 patients should be enrolled in each group. Considering a 15% dropout rate, 92 participants are needed in each group, thus expanding the sample size to 100 cases per group.

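### The alcohol exclusion is printed as 210 g/day (men) and 140 g/day (women): implausibly high for its purpose, probably a day/week slip, and it must be reconciled with the approved protocol

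*Protocol article*

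**What the plan says.** Under Eligibility criteria, item (2) of the Exclusion Criteria is "History of heavy alcohol consumption (alcohol intake >210 g/day for men", followed by a limit of more than 140 g/day for women. The daily unit is printed for both sexes. No other visible text gives an alcohol limit, a weekly unit or an exclusion for alcohol-related liver disease.

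The next exclusion covers steatosis with another non-metabolic cause: "Drug-induced secondary hepatic steatosis (e.g., tamoxifen, hormones".

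Entry to the MAFLD group has two steps. The first is "Diagnosis of hepatic steatosis confirmed by abdominal ultrasound, Fibroscan, or liver steatosis measurement via MRI". The second is "Additionally, the patient must meet one of the following three conditions": BMI of at least 23 kg/m², diabetes, or at least two metabolic abnormalities in lean or normal-weight patients. Neither step, as written, separates alcohol-related from metabolic fat. Figure 2, which sets out the MAFLD diagnostic process, is not available to this review.

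The primary analysis (Statistical methods, Primary outcomes) is Kaplan–Meier with a log-rank test. The Discussion names age, gender and baseline liver function as factors the team will try to control, and lists lifestyle habits among possible unmeasured influences.

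**The concern.** The criterion labels its target as heavy drinking and stands next to the exclusion of drug-induced steatosis, so its evident purpose is to keep non-metabolic fatty liver out of the comparison. A limit of 210 g or 140 g a day does this poorly: a man at 200 g/day or a woman at 130 g/day is not excluded.

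This matters because MAFLD is the exposure under study and the groups are not randomised. Steatosis decides group membership. If alcohol causes some of that steatosis, drinkers will tend to collect in the MAFLD group, and any effect of alcohol on HBsAg clearance would be mixed with the effect of MAFLD. The exclusion is the only visible control on alcohol: the log-rank test does not adjust for it, and the named confounders do not include it.

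**Working it through.** **Inputs.** Limits of 210 and 140 g/day (Exclusion Criteria, item 2). Clearance of 35% (CHB) and 60% (CHB with MAFLD), power 0.90, α = 0.05, 79 per group before dropout, 15% dropout, 100 enrolled per group (Sample size). Ethanol density of 0.789 g/mL is a physical constant, not from the article. A two-sided test is assumed, as sidedness is not stated.

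**Step 1: what the printed limits mean.**

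| | Men | Women |
|---|---|---|
| Printed limit, g/day | 210 | 140 |
| Per week (× 7) | 1,470 g | 980 g |
| As 5% beer: g ÷ (0.789 × 0.05) | 5.3 L/day | 3.5 L/day |
| As 40% spirit: g ÷ (0.789 × 0.40) | 0.67 L/day | 0.44 L/day |
| Same number read as a weekly limit (÷ 7) | 30 g/day | 20 g/day |

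Both numbers divide by 7 to a round figure. That fits a day/week slip but does not prove one. The two readings differ by a factor of 7.

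**Step 2: does another written rule remove drinkers below the limit?** The drug-induced steatosis exclusion does not. The exclusions for cirrhosis and for other serious organic or psychiatric disease would remove some severe cases, but they set no drinking limit. The MAFLD definition needs only imaging steatosis plus one metabolic condition. So a man drinking 200 g/day, with steatosis and a BMI of 23 or more, passes item (2) and meets the MAFLD definition.

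**Step 3: how large could the effect be?** The article gives neither the share of drinkers nor their clearance rate, so this is an illustration, not an estimate.

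The plan's own figure is reproduced first. The unpooled formula gives n = (1.960 + 1.282)² × (0.35 × 0.65 + 0.60 × 0.40) ÷ 0.25² = 78.6, or 79 as stated ("The calculation indicated that 79 patients should be enrolled in each group"). The alcohol point does not change it.

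Now assume that a fraction f of the MAFLD group has alcohol-driven steatosis and clears at the CHB rate of 35%. The MAFLD group rate is then p₂ = 0.60 − 0.25f. With 100 × 0.85 = 85 evaluable per group and the pooled-null formula,

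power = Φ{ [ (p₂ − 0.35)√85 − 1.960√(2p̄(1 − p̄)) ] ÷ √(0.35 × 0.65 + p₂(1 − p₂)) }, where p̄ = (0.35 + p₂)/2.

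| f | p₂ | Difference, percentage points | Power |
|---|---|---|---|
| 0 | 0.6000 | 25.00 | 91% |
| 5% | 0.5875 | 23.75 | 88% |
| 10% | 0.5750 | 22.50 | 84% |
| 20% | 0.5500 | 20.00 | 75% |
| 30% | 0.5250 | 17.50 | 64% |

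Under this assumption the result is dilution: modest for small f, material for large f. A different clearance rate among drinkers would change the size of the bias and could change its direction.

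**The case against.** The strongest reply is that this is a printing error with no consequence for the data. If the approved protocol states a weekly limit and the sites screened with it, no patient was admitted wrongly and only the article needs correcting. That stands as a possibility. A reader might infer from the printed limit that heavy drinkers have entered the MAFLD group. The article does not support this, because it does not show which limit was applied.

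A reader might also call such patients misclassified. That does not follow either. The article defines MAFLD positively, by steatosis plus a metabolic condition, and its visible text sets no alcohol ceiling in that definition. A drinker with steatosis and a BMI of 23 or more is MAFLD as defined. The accurate description is mixed cause, and the statistical issue is confounding.

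There are partial safeguards. Figure 2 may contain an alcohol step, and its absence here cannot be held against the plan. A physician checks every criterion at screening. Drinkers without steatosis may enter the CHB group, so the imbalance is plausible rather than certain. None of these supplies a usable limit in the text, and a different limit in Figure 2 would itself conflict with item (2).

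**Conclusion.** The concern holds as a probable unit error in an eligibility criterion. The printed limits, equal to 1,470 and 980 g a week, defeat the stated purpose of excluding heavy drinking. If they were applied literally, alcohol could confound an unadjusted, non-randomised comparison.

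The size cannot be estimated from the article. It ranges from nothing, if a weekly limit was used at screening, to an amount that depends on an unknown share of drinkers and their unknown clearance rate. Two stronger readings are not supported. One is that the criterion excludes almost nobody, which would need a drinking distribution that the article does not give. The other is that the MAFLD effect becomes uninterpretable: in the illustration above, 5% to 10% affected patients lower power from 91% to between 88% and 84%. The conclusion rests on the printed text and on no other alcohol limit being visible. It does not rest on that illustration.

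**What to change.** 1. Reconcile the printed unit with the approved protocol, the case report form and Figure 2, and correct the text. This review does not say which limit is right.
2. Report which limit each of the four centres applied at screening.
3. Only if the daily limit was in fact applied: review the recorded alcohol intake of enrolled patients, and add a sensitivity analysis of the primary outcome that either leaves out those above the reconciled limit or adjusts for intake.

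The cost is a short correction, a query to four sites and, if step 3 is triggered, one extra analysis with possibly a few fewer patients. Step 3 depends on intake having been recorded in enough detail. The Recruitment section mentions review of symptoms, laboratory results and imaging, and the case report form is not shown, so this should be checked early. Enrolment began on June 1, 2024, so some patients will already have been screened under whichever limit is in use.

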### Intervention description

1 Peg-IFN dosing:(1) For patients with body weight ≥ 70 kg: 180 μg once a week, subcutaneous injection.(2) For patients with body weight < 70 kg: 135 μg once a week, subcutaneous injection.2 Duration:(1) The treatment duration is 48 weeks.(2) If the patient achieves HBsAg serologic conversion (HBsAb >300 IU/L) and maintains this response for 24 weeks, the treatment can be discontinued for observation, even if the full 48 weeks have not been completed.

### Criteria for discontinuing or modifying allocated interventions

Discontinuation Due to Special Requirements: If the patient requires discontinuation of Peg-IFN due to special circumstances (e.g., trauma, surgery, personal preference), the treatment can be resumed once the conditions for using Peg-IFN are met again. Serious Adverse Events (SAEs): If SAEs occur, the necessity to discontinue Peg-IFN will be assessed, and treatment will be adjusted accordingly.

### Strategies to improve adherence to the intervention

In this study, we provided around-the-clock (24-h) health consultation services to ensure that patients could access professional support and guidance from healthcare providers at any time. Our team offered continuous attention and necessary assistance throughout the study, addressing a range of needs including study-related treatment guidance, management of adverse drug reactions, monitoring of virological breakthroughs, and general health inquiries from patients.

### Relevant concomitant intervention permitted or prohibited during the trial

Adverse effects of PEG-IFNα-2b include transient, early-onset flu-like symptoms such as fatigue, fever, muscle aches, headache, chills, and joint pain, which typically resolve within a few days to a few weeks. Some patients may experience reduced appetite, nausea, abdominal pain, and diarrhea. Additional symptoms include dizziness, hair loss, weight loss, visual disturbances, dry and itchy skin, injection site discomfort, and rashes. Furthermore, patients may encounter cognitive and psychological issues, such as difficulty concentrating, memory impairment, anxiety, irritability, and sleep disorders. Temporary changes in laboratory parameters, including decreases in white blood cell, neutrophil, and platelet counts, as well as alterations in liver biochemical function, have also been observed. PEG-IFNα-2b can cause thyroid dysfunction, exacerbate diabetes, or induce certain immune system disorders. To address these adverse effects, a dedicated team conducts regular follow-ups and provides timely interventions. Management strategies for adverse effects may involve discontinuing therapy, dose modifications, or targeted supportive treatments for specific side effects.

### Outcome

Primary outcome indicators: 48-week HBsAg clearance rate. Secondary outcome indicators: 48-week HBsAg quantitative decline, HBV DNA undetectable rate, HBsAg serologic conversion rate, Peg-IFN adverse reactions.

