### Participant timeline

A Case Report Form (CRF) form will be established and completed for each enrolled patient, with follow-up visits scheduled every 12 weeks (±2 weeks) at baseline and throughout the treatment period. Clinical symptoms and signs will be observed during each follow-up visit, and peripheral blood PBMC and plasma specimens will be collected and stored at −80°C for future research. The clinical test items at the follow-up visit are shown in Figure 3.

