### Statistical methods for primary and secondary outcomes

#### Primary outcomes

The Kaplan–Meier method was used to estimate the cumulative incidence of HBsAg seroclearance, and the log-rank test was used to compare the cumulative probabilities of different subgroups.

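### The primary outcome is a week-48 clearance proportion, but the only stated primary analysis is a Kaplan–Meier curve with a log-rank test; on actual visit dates the reported group rates can be well off

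*Protocol article*

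**What the plan says.** - Outcome section: "Primary outcome indicators: 48-week HBsAg clearance rate". This is one quantity at one time.
- Sample size section: earlier work by the same team "resulted in HBsAg clearance rates of 35 and 60%, respectively" in CHB and CHB with MAFLD. The calculation used "the test module for two independent sample rates in PASS 11.0", with "Setting the test level at *α* = 0.05" and "the power of the study (1-*β*) at 0.90". It gives 79 per group, 92 after 15% dropout, and 100 as the final figure.
- Trial design section: patients are sorted into responders and non-responders once treatment is over, which is also a binary status.
- Statistical methods, Primary outcomes: the Kaplan–Meier method "was used to estimate the cumulative incidence of HBsAg seroclearance", and a log-rank test compares the curves. No read-off time is named, and no comparison of week-48 proportions appears.
- Participant timeline: "follow-up visits scheduled every 12 weeks (±2 weeks" either side. Additional consent provisions lists the visits as baseline and weeks 12, 24, 36 and 48, counted from enrolment. Week 48 is the last one listed.
- The article does not say whether event time is the nominal visit or the calendar date, whether clearance must be confirmed, or how a patient who clears and then tests positive again is classed.

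**The concern.** The endpoint and the power calculation describe a proportion at week 48. The stated analysis describes time to first detected clearance. The two need not give the same number, for two reasons.

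**Dates.** Clearance is detected only at visits, and the last visit can fall anywhere in weeks 46–50. On calendar dates, the last clearances and the censoring of all remaining non-clearers interleave within the same four weeks. Read at day 336, the curve misses clearances found at visits held later in the window. Read at the end of the window, it is too high, because patients still positive at an early final visit leave the risk set before later clearances are counted.

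**Reversion.** A first-event curve never takes an event back. A patient who clears at week 24 and is positive at week 48 remains a success, although the article treats clearance as its marker of clinical cure.

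At stake is the headline figure, the 48-week clearance rate in each group, which clinicians would quote.

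**Working it through.** **1. The plan's own figure.** Unpooled two-proportion formula, two-sided α = 0.05 (the article does not state sidedness), power 0.90:

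n = (0.35×0.65 + 0.60×0.40) × (1.960 + 1.2816)² / 0.25² = 0.4675 × 10.51 / 0.0625 = 78.6, so 79.

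This matches the stated 79 and confirms that the study was sized on a proportion.

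**2. Does the mismatch harm the sample size?** Under proportional hazards the same rates give HR = ln 0.40 / ln 0.65 = 2.13. Schoenfeld events: 4 × 3.2416² / (ln 2.13)² = 73.8, so 74. Expected events at 79 per group: 79 × (0.35 + 0.60) = 75. With 85 evaluable per group (100 less 15%), power is 91% for two proportions (pooled formula) and 92% for the log-rank test. N is adequate either way.

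**3. Nominal visit times.** With no reversion and non-informative dropout, Kaplan–Meier at week 48 returns 35% and 60%, with or without 15% dropout. There is no bias.

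**4. Actual dates, by hand.** Assume a constant clearance hazard with 60% cleared by week 48. Uncleared after week 36: 0.40^(36/48) = 0.503. Cleared between weeks 36 and 48: 0.503 − 0.400 = 0.103, which is 20.5% of those still at risk. Spread the final visits evenly over the 29 days of the window.
- At day 336 about half the final visits have taken place. The curve reads 1 − 0.503 × 0.5^0.205 = 56.4%.
- On the last day the curve reads 1 − 0.503 × ∏(1 − 0.205/j), j = 1 to 29, which is about 78%.

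The truth is 60%.

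**5. Actual dates, by simulation.** Weibull clearance times scaled to 35% and 60% at day 336, visits at days 84, 168, 252 and 336 with uniform ±14 days, 100 per group, 1,000 trials:

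| Weibull shape | Day 336: 35% / 60% | Difference | End of window: 35% / 60% | Difference |
|---|---|---|---|---|
| 1 | 32.3 / 56.4 | 24.1 | 53.5 / 78.7 | 25.2 |
| 1.5 | 31.0 / 54.0 | 23.0 | 59.3 / 84.1 | 24.8 |
| 2 | 29.8 / 52.1 | 22.3 | 63.3 / 86.8 | 23.5 |

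The errors are 2.7 to 7.9 points low at day 336 and 18.5 to 28.3 points high at the end of the window. With exponential times and 15% dropout, the low-side error can be nearer 2 points (32.8% against 35%). The true difference is 25 points, and both groups shift together.

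**6. Reversion (rate assumed; the documents give none).** With exponential times, 49.7% and 27.6% of the groups clear by week 36. If 5%, 10% or 20% of these are positive again at week 48, the true week-48 proportions are about 57.5%, 55% or 50% where the curve still shows 60%, and about 33.5%, 32% or 29% where it shows 35%. For example, 60 − 0.10 × 49.7 = 55.0.

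**7. Dropout.** Counting 15% dropouts as not cleared gives 0.85 × 60 = 51% and 0.85 × 35 = 30%. That is a different estimand from the censored curve, so a rule is needed.

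**The case against.** The strongest reply is that no bias has been shown. The article does not say that calendar dates will be used. Time scale, read-off point and confirmation rule are ordinary SAP content, and the SAP is not shown. A 48-week rate can also be read as cumulative clearance by week 48, which suits a Kaplan–Meier curve. The largest errors need actual dates and a curve read at week 50, although the outcome names week 48; their upper ends also need a rising clearance hazard that nothing in the documents supports. The study's question is the comparison between groups, and that hardly moves: in a simulation on jittered dates with 85 per group, the log-rank test kept about 5% type I error and about 90% power. For dropout, the missing-data section already plans multiple imputation, sensitivity analyses for data not missing at random and a drop-out analysis.

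Most of this stands, and it limits the point. A reader might infer that the plan necessarily misreports the 48-week rate, or that the sample size is invalid. The documents support neither: nominal coding removes the date bias, and N is adequate under both analyses. What remains is the conflict in the text. The endpoint and sample size call for a proportion at one time, and the primary analysis section offers no estimate or test of it. Coding details in an SAP could remove the date problem, but would not by themselves reconcile those sections or settle how reverters are counted.

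**Conclusion.** The point holds as an inconsistency that should be fixed, not as a demonstrated error in the result. The stated primary analysis does not directly estimate or test the stated primary outcome. If actual visit dates are used, each group's 48-week rate can be about 2–8 points low at day 336, or roughly 20–30 points high at the end of the window. These sizes assume final visits spread evenly over ±14 days and Weibull shapes from 1 to 2. On nominal visits with no reversion and non-informative dropout the error is zero. In either case the between-group difference (about 22–25 points against a true 25) and the power are largely preserved. First-event counting would overstate week-48 clearance if any patient reverts, by an amount the documents do not allow one to estimate.

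**What to change.** 1. Make the primary analysis a comparison of HBsAg status at the nominal week-48 visit (window weeks 46–50), counted from one stated time origin, such as enrolment or first injection. Report the risk difference with 95% CI.
2. Classify patients who clear and become positive again by their week-48 status.
3. Handle missing week-48 results with the multiple imputation already planned, and add a sensitivity analysis that counts dropouts as not cleared.
4. Keep time to first clearance as a supportive analysis, on nominal visits 12, 24, 36 and 48, with a discrete-time or interval-censored model.

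The alternative is to redefine the primary outcome as cumulative first clearance by week 48, with a stated confirmation rule, and to say so in the Outcome and Sample size sections.

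The cost is wording only. The sample size needs no change: power is about 91% with 85 evaluable per group. The change should be made before efficacy data are examined, since the Interim analyses section describes an initial comparison between groups during 2025 among patients who have completed 48 weeks.

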## Abstract

**Introduction:**

The incidence of chronic hepatitis B (CHB) combined with metabolism-associated fatty liver disease (MAFLD) is increasing annually, and the presence of MAFLD may influence the clinical assessment of viral activity and transaminase levels. However, it remains unclear whether MAFLD impacts the achievement of clinical cure in CHB patients treated with polyethylene glycol interferon (Peg-IFN).

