### Recruitment

Participants will be recruited from four medical centers in Beijing and Hebei, China: Beijing You’an Hospital of Capital Medical University, Fifth Medical Center of General Hospital of the People’s Liberation Army, Beijing Ditan Hospital of Capital Medical University, and Baoding People’s Hospital. Each hospital will have a study coordinator to facilitate and coordinate the trial. Patients will be informed of the study’s purpose, procedures, and potential risks and benefits. Written informed consent will be obtained from all participants. They will also be allowed to withdraw from the trial at any time without any consequences.

Patients will be invited to participate in this study shortly after diagnosis. At the screening follow-up, a clinically experienced researcher (physician) will confirm eligibility for enrollment by reviewing symptoms, laboratory results, and imaging such as ultrasound or CT, ensuring that each inclusion and exclusion criterion is met. Recruitment will occur over 24 months, from January 2024 to December 2025.

No patients or members of the public other than professional clinicians and researchers were involved in the design, conduct, reporting, or dissemination plans for this study.

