### Interim analyses

The superior CHB cohort and the CHB combined MEFLD cohort continued to be maintained between 2025–01 and 2025–12. Regular follow-up observations were made every 12 weeks to record HBsAg and HBsAb, HBeAg and HBV DNA data and adverse events. For some of those who completed 48 weeks of antiviral therapy, the difference in efficacy between the two groups was initially analyzed.

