### Management of adverse events and health changes during the study

If, during the study, a patient experiences any discomfort, new changes in their condition, or any unexpected events, whether related to the study or not, they must promptly notify the relevant research center physician. The physician will assess the situation and provide appropriate medical treatment. The treatment measures may include discontinuation of medication, dose reduction, or other supportive therapies. Adverse reactions during interferon therapy are considered normal; most symptoms will resolve after appropriate management. The research team will closely monitor these reactions and provide timely and appropriate interventions.

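### The only safety outcome counts reactions attributed to Peg-IFN by clinicians who know MAFLD status, so a CHB versus CHB+MAFLD comparison of liver-test and glycaemic events may be distorted

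*Protocol article*

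**What the plan says.** The Outcome section gives one safety item, at the end of the secondary list: "Secondary outcome indicators: 48-week HBsAg quantitative decline, HBV DNA undetectable rate, HBsAg serologic conversion rate, Peg-IFN adverse reactions". The Abstract and the Objectives both name safety of Peg-IFN as an aim.

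The Study setting section states: "This prospective, multicenter, open cohort study will include HBV-infected patients from four large tertiary hospitals in North China". The groups are 100 patients with CHB and 100 with CHB and MAFLD. Under Recruitment, the physician "will confirm eligibility for enrollment by reviewing symptoms, laboratory results, and imaging such as ultrasound or CT", so MAFLD status is known from the start.

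Three places bear on competing causes:
- The Abstract says that "the presence of MAFLD may influence the clinical assessment of viral activity and transaminase levels".
- The section on concomitant interventions lists altered liver biochemistry among observed Peg-IFN effects and adds that "PEG-IFNα-2b can cause thyroid dysfunction, exacerbate diabetes, or induce certain immune system disorders".
- The Eligibility criteria require steatosis for the MAFLD group and make diabetes one of three further conditions, any one of which qualifies.

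Two places describe wider recording. The Interim analyses section has visits every 12 weeks "to record HBsAg and HBsAb, HBeAg and HBV DNA data and adverse events", with no relatedness condition. The section on managing adverse events asks patients to report discomfort, changes in condition "or any unexpected events, whether related to the study or not".

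**The concern.** An outcome limited to drug-attributed events passes through a clinician's judgement before it is counted. That does little harm when the judgement is equally hard in both groups. Here the exposure under study is itself a possible cause of some of the events. Faced with a raised transaminase, a clinician has steatosis as an additional explanation in the MAFLD group. Faced with worse glucose, pre-existing diabetes is an additional explanation, and diabetes is one of the criteria used to form that group. Whether an event counts can therefore depend on the group the patient is in, and a larger sample would not remove this.

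The Objectives promise guidance on selecting candidates for Peg-IFN. If labelling alone made Peg-IFN look equally safe or safer in MAFLD for hepatic and metabolic events, or less safe, that would pass into the guidance.

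**Working it through.** The article gives no figure for the safety outcome, so there is none to reproduce. The check has two parts.

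**1. Does the text support differential attribution, and for which events?**

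| Listed Peg-IFN effect | Link to MAFLD in the article |
|---|---|
| Altered liver biochemistry | Yes: the Abstract says MAFLD may affect how transaminases are assessed |
| Worsening diabetes | Yes: diabetes is one of the MAFLD criteria |
| Flu-like, gastrointestinal, skin, hair, visual, psychological, blood-count, thyroid and immune effects | None stated |

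The overlap is therefore confined to two event types. It is also a matter of degree. Diabetes counts towards MAFLD only together with steatosis, so the CHB group may include diabetic or overweight patients without steatosis, and CHB itself can disturb liver tests in both groups.

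**2. How large could the distortion be?** Apart from the group size, every input below is an assumption.

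- True per-patient incidence *p*, equal in both groups
- Share attributed to Peg-IFN: *a*₁ = 0.90 in CHB; *a*₂ = 0.80, 0.70 or 0.60 in CHB+MAFLD
- *n* = 100 per group (Study setting)
- Spurious gap = *p*(*a*₁ − *a*₂)
- SE = √{[*r*₁(1−*r*₁) + *r*₂(1−*r*₂)]/*n*}, with *r* = *p·a*
- P(false p<0.05) = Φ(gap/SE − 1.96) + Φ(−gap/SE − 1.96)

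Worked case, *p* = 0.15 and *a*₂ = 0.70: *r*₁ = 0.135 and *r*₂ = 0.105. The gap is 0.030, SE = √(0.00211) = 0.0459, and gap/SE = 0.65. The probability is Φ(−1.31) + Φ(−2.61) ≈ 0.10.

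| True incidence | Gap, points (*a*₂ = 0.80 / 0.70 / 0.60) | P(false p<0.05) |
|---|---|---|
| 15% | 1.5 / 3 / 4.5 | 0.06 / 0.10 / 0.17 |
| 30% | 3 / 6 / 9 | 0.08 / 0.17 / 0.33 |
| 40% | 4 / 8 / 12 | 0.09 / 0.23 / 0.46 |

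The 15% row stands for the overlapping event types alone. The 30% and 40% rows apply the lower attribution to all events, which is an upper-end case. Suppose overlapping events are a share *s* of all events, are attributed at 90% in CHB, and are all reassigned in MAFLD. Overall attribution then falls by 0.90*s*. A fall to 80%, 70% or 60% needs *s* = 0.10/0.90 = 11%, 0.20/0.90 = 22% or 0.30/0.90 = 33%. In a per-patient count those patients must also have no other attributed reaction, since one with fever or a low neutrophil count is still counted.

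If clinicians over-attribute in MAFLD instead, the sign of every gap reverses.

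**The case against.** The strongest reply is that the outcome line is a label rather than an attribution rule. The article also speaks of adverse effects, adverse events and adverse reactions without separating them, and it records events without a relatedness condition. How reactions are defined and tabulated may be settled in the full protocol or the analysis plan, neither of which is shown. This stands in part: the absence of a causality scale or an assessor rule is no finding, and none is claimed. But the outcome that the article does state is the drug-attributed one.

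Second, no between-group safety test is written out. The comparisons that are named concern efficacy, HBsAg clearance and T cells. This also stands. A safety comparison is the natural reading of a two-group design that lists safety beside the efficacy outcomes, but it remains a reading, and the conclusion is conditional on it.

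Third, all-cause counting has a weakness of its own. Both groups receive Peg-IFN and there is no untreated control, so all-cause events in MAFLD patients include some that belong to MAFLD, and Peg-IFN could look worse there. This is a real cost. Counting only events new or worsened from the patient's own baseline reduces it without removing it, and for that reason attributed reactions should still be shown.

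A reader might infer more: that the safety comparison is biased in favour of MAFLD, or that MAFLD supplies another cause in one group only. The documents support neither. They give no attribution rates and no direction, and CHB patients can also have competing causes.

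**Conclusion.** The point holds as a risk confined to liver-biochemistry and glycaemic events. If the two groups are compared on attributed reactions, the result may be distorted for those events, because clinicians know MAFLD status and MAFLD patients more often have a competing explanation. Size and direction are unknown. On the assumed inputs, a 10-point difference in attribution for events with 15% incidence is almost harmless (false-positive chance 0.06 against a nominal 0.05), while a 30-point difference is material (0.17). The larger probabilities, 0.33 and 0.46, require lower attribution across all events and should not be quoted as the expected effect.

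This rests on reading the outcome as drug-attributed, as worded, and on a between-group safety comparison being intended. It concerns a secondary outcome, but the only one for safety, and the correction is cheap enough to be worth making.

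**What to change.** In the Outcome section, define the between-group safety outcome as all adverse events that are new or worsened from the patient's own baseline, regardless of judged cause. Grade the liver, blood-count and thyroid tests against baseline; these are already scheduled at baseline and weeks 12, 24, 36 and 48 under Additional consent provisions. Glucose is not in that list; whether it is in the visit schedule (Figure 3) cannot be seen here, so confirm what glycaemic data will be available.

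Report per-patient incidence in each group and the risk difference with a 95% confidence interval, overall, for serious events, and for events leading to interruption or stopping of Peg-IFN. Show Peg-IFN-attributed reactions alongside as supportive information.

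The cost is mainly wording and some extra tabulation, since adverse events are already recorded every 12 weeks. Reported counts will be higher and will include some background MAFLD events. The report should state that, without an untreated control, a group difference is not a pure Peg-IFN effect.
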